# Varied overground walking-task practice versus body-weight-supported treadmill training in ambulatory adults within one year of stroke: a randomized controlled trial protocol

**DOI:** 10.1186/1471-2377-11-129

**Published:** 2011-10-21

## Abstract

**Background:**

Although task-oriented training has been shown to improve walking outcomes after stroke, it is not yet clear whether one task-oriented approach is superior to another. The purpose of this study is to compare the effectiveness of the Motor Learning Walking Program (MLWP), a varied overground walking task program consistent with key motor learning principles, to body-weight-supported treadmill training (BWSTT) in community-dwelling, ambulatory, adults within 1 year of stroke.

**Methods/Design:**

A parallel, randomized controlled trial with stratification by baseline gait speed will be conducted. Allocation will be controlled by a central randomization service and participants will be allocated to the two active intervention groups (1:1) using a permuted block randomization process. Seventy participants will be assigned to one of two 15-session training programs. In MLWP, one physiotherapist will supervise practice of various overground walking tasks. Instructions, feedback, and guidance will be provided in a manner that facilitates self-evaluation and problem solving. In BWSTT, training will emphasize repetition of the normal gait cycle while supported over a treadmill, assisted by up to three physiotherapists. Outcomes will be assessed by a blinded assessor at baseline, post-intervention and at 2-month follow-up. The primary outcome will be post-intervention comfortable gait speed. Secondary outcomes include fast gait speed, walking endurance, balance self-efficacy, participation in community mobility, health-related quality of life, and goal attainment. Groups will be compared using analysis of covariance with baseline gait speed strata as the single covariate. Intention-to-treat analysis will be used.

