Physiotherapists trained to perform the standardized outcome measures will measure outcomes. Assessors will be blinded to the participant's intervention assignment and study hypotheses, limiting the potential for expectation bias. Participants will be instructed not to reveal their group assignment to the assessor.

Outcome assessment domains, tools and timing are summarized in Table 2.

**Table 2 T2:** Outcome domains, measures and timing of assessments

*ICF*	*Domain*	*Instrument*	*Screening/Baseline*	*Post -Intervention*	*Follow-up*
Personal and Environmental Factors	Stroke details	Interview, health record review	X		
	Comorbidities		X		
	Living situation		X		
	Gait aid		X	X	X
	Physiotherapy		X	X	X
	Fall history		X	X	X
	Adverse events		X	X	X
Body Structures/Function	Motor recovery	Chedoke-McMaster Stroke Assessment	X		
	Cognition	Mini Mental Status Examination	X		
	Depression	Geriatric Depression Scale Short form-15	X		
Activity	Walking speed	5 metre walk test	X	X	X
	Walking endurance	Six Minute Walk Test	X	X	X
	Dynamic balance	Functional Balance Test	X	X	X
	Balance self-efficacy	Activities-specific Balance Confidence Scale	X	X	X
	Goal attainment	Patient Specific Functional Scale	X	X	X
Participation	Walking independence	Modified Functional Ambulation Categories	X	X	X
	Daily walking activity	Step Watch 3.0 step activity monitor	X	X	X
	Mobility participation	Life Space Questionnaire	X	X	X
	Health related quality of life	Stroke Impact Scale 3.0	X	X	X

ICF = International Classification of Function domains

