### Statistical Analysis

The trial results will be reported in accordance with the CONSORT criteria [http://www.consort-statement.org]. The flow of patients in the trial will be summarized using a flow-diagram. The baseline characteristics and outcomes scores of the patients will be analyzed using descriptive statistics reported by group as mean (standard deviation [SD]) or median (first quartile [Q1], third quartile [Q3]) for continuous variables depending on the distribution and count (percent) for categorical variables. Intention to treat analysis technique will be used for the primary analysis [71]. Missing data will be handled through multiple imputation technique [72]. All statistical tests will be performed using two-sided tests at the 0.05 level of significance. The Tukey's HSD method will be used to adjust the level of significance for testing for secondary outcomes. For all models, the results will be expressed as estimate of mean difference (or odds ratios for binary outcomes), standard errors, corresponding two-sided 95% confidence intervals and associated p-values. P-values will be reported to three decimal places with values less than 0.001 reported as < 0.001. Adjusted analyses will be performed using regression techniques to investigate the residual impact of key baseline characteristics on the outcomes (i.e. age, time since stroke onset, comfortable gait speed, and training site). Goodness-of-fit will be assessed by examining the residuals for model assumptions and chi-squared test of goodness-of-fit. All analyses will be performed using SPSS version 16.0 for Windows or SAS 9.2 (Cary, NC).

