#### Primary Analysis

The post-intervention (T2) self-selected overground walking speed for the MLWP and BWSTT groups will be compared using analysis of covariance. The two factors will be intervention group (intervention or control) and baseline speed stratum (i.e. slow or fast).

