#### Secondary Analysis

Mixed design analysis of variance will be used to compare the two groups' baseline, post-intervention and follow-up scores on all other secondary measures. The two factors will be time and group. Descriptive statistics (i.e. means, or frequencies) will be used to present data related to adverse and serious adverse events by groups. Any apparently significant differences between groups will be analysed for significance using chi square statistics. In an effort to describe the two interventions, the mean number of steps taken per session will be counted in a convenient sub-sample of participants using the step activity monitors. Independent samples t-test statistic will be used to compare the mean number of steps taken per session by the two groups during treatment sessions.

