**2) Secondary (T2, T3)**			
Secondary outcomes			
a) Fast walking speed	MLWP > BWSTT	Fast Gait Speed (c)	ANCOVA
b) Walking endurance	MLWP > BWSTT	Six minute walk test(c)	ANCOVA
c) Balance and walking related self-efficacy	MLWP > BWSTT	Activities-specific Balance Confidence Scale (c)	ANCOVA
d) Dynamic balance	MLWP > BWSTT	Functional Balance Test(c)	ANCOVA
e) Mobility participation	MLWP > BWSTT	Life Space Questionnaire (c)	ANCOVA
f) Health-related quality of life	MLWP > BWSTT	Stroke Impact Scale 3.0 (c)	ANCOVA
g) Goal attainment	MLWP > BWSTT	Patient Specific Function Scale(c)	ANCOVA
h) Walking participation	MLWP < BWSTT	Mean daily step activity	ANCOVA
i) Training staff requirement	MLWP < BWSTT	Total number of trainers/number of training sessions (c)	T-test
j) Meaningful change in gait speed of ≥ 0.14 m/s	MLWP > BWSTT	Comfortable gait speed change score T2-T1 ≥ 0.14 m/s)(b)	Chi-square test
Adverse events (count)			
a) Falls during session		Therapist report (b)	Chi-square test
b) Injury during session		Therapist report (b)	Chi-square test
c) Falls between session		Patient report (b)	Chi-square test
d) Myocardial Infarction		Patient report/health record (b)	Chi-square test
e) New stroke		Patient report/health record (b)	Chi-square test
f) Hospitalization		Patient report/health record (b)	Chi-square test
g) Death (all causes)		Health record/Physician (b)	Chi-square test

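### The protocol gives two conflicting models for the secondary outcomes, and neither uses the outcome's own baseline score as a covariate, although that score is collected.

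*Protocol article*

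**What the plan says.** All references are to the Protocol article.

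- **Abstract, Methods/Design.** Straight after naming the secondary outcomes: "Groups will be compared using analysis of covariance with baseline gait speed strata as the single covariate".
- **Primary Analysis.** The ANCOVA of post-intervention comfortable speed has the same structure: "The two factors will be intervention group (intervention or control) and baseline speed stratum (i.e. slow or fast".
- **Table 3, secondary block.** Rows a to h (fast speed, endurance, self-efficacy, balance, life space, quality of life, goals, daily steps) are assigned ANCOVA at T2 and T3. The table names no covariate.
- **Secondary Analysis.** "Mixed design analysis of variance will be used to compare the two groups' baseline, post-intervention and follow-up scores on all other secondary measures". Then: "The two factors will be time and group". There is no stratum term, and nothing says whether the group effect or the group-by-time interaction is the test.
- **Statistical Analysis.** The additional adjusted regressions list "age, time since stroke onset, comfortable gait speed, and training site". Apart from comfortable gait speed, no outcome's own baseline appears.
- **Outcomes and Table 2.** The measures behind rows a to h, for example the "Activities-specific Balance Confidence Scale", are all scheduled at baseline, post-intervention and follow-up.
- **Outcomes (opening sentence) and Sensitivity Analyses.** Efficacy is to be judged on change from baseline, and a generalized estimating equations (GEE) analysis covers all outcomes at baseline, T2 and T3.

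**The concern.** A reader cannot tell which model produces the reported result for a secondary outcome. ANCOVA on the stratum and a time-by-group ANOVA estimate the treatment effect differently and can disagree.

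For most of rows a to h, the stratum is a two-level version of a different variable's baseline. It removes only the part of the outcome's variance that comfortable gait speed explains. The outcome's own baseline score usually explains more, it is already measured, and no planned model conditions on it.

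The Background section hypothesises superiority on the secondary measures as well, while the Sample size section sizes the trial only for gait speed. Precision on these outcomes is therefore scarce. Without own-baseline adjustment, intervals are wider than the data allow and a chance baseline difference passes into the estimate.

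**Working it through.** **The plan's own figure.** Two-sample formula, difference 0.14 m/s, SD 0.19 m/s, two-sided 0.05, 80% power: n = 2 × [0.19 × (1.960 + 0.842) / 0.14]² = 28.9, so 29 per group. Then 29 / 0.83 = 34.9, so 35 per group and 70 in total. This reproduces the plan. It concerns the primary outcome only and is used here for n = 29 evaluable per arm.

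**Assumptions (not in the document).** Outcome variance 1 at each visit; true effect 0.5 SD; r = correlation of an outcome's baseline with its later score, 0.5 to 0.8; g = correlation of the outcome with comfortable gait speed, 0.3 to 0.5; 30% to 50% of participants in the slow stratum.

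**Residual variances.**

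1. Stratum only. The stratum–outcome correlation is a = k × g, with k = φ(z)/√[p(1−p)], which is 0.759 at p = 0.3 and 0.798 at p = 0.5. So a runs from 0.228 to 0.399, and the variance 1 − a² from 0.95 down to 0.84.
2. Stratum plus own baseline, with a also the stratum–baseline correlation: 1 − (a² + r² − 2a²r)/(1 − a²). This gives 0.70–0.74 at r = 0.5, 0.49–0.51 at r = 0.7 and 0.35–0.36 at r = 0.8.
3. Mixed ANOVA, baseline-to-T2 contrast: 2(1 − r) = 1.0, 0.6 and 0.4.
4. Mixed ANOVA, group main effect over three visits with equal correlations: variance (1 + 2r)/3 = 0.67, 0.80 and 0.87. With the effect present at T2 and T3 only, it shrinks to (0 + 0.5 + 0.5)/3 = 0.33 SD.

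**Power, two-sample t, 29 per arm.**

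| Analysis | r = 0.5 | r = 0.7 | r = 0.8 |
|---|---|---|---|
| ANCOVA, stratum only | 48–53% | 48–53% | 48–53% |
| ANCOVA, stratum + own baseline | 59–61% | 75–76% | 88% |
| Mixed ANOVA, baseline-to-T2 contrast | 46% | 68% | 84% |
| Mixed ANOVA, group main effect | 33% | 29% | 27% |

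**Equivalent sample size.** The ratio of variance 1 to variance 2 is 1.20–1.29 at r = 0.5, 1.71–1.88 at r = 0.7 and 2.39–2.65 at r = 0.8.

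**Chance imbalance.** One standard error of a baseline difference is √(2/29) = 0.26 SD. Left unadjusted at r = 0.7, it moves the estimate by about 0.7 × 0.26 = 0.18 SD (slightly less within strata).

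**The case against.** A reader might infer that the secondary outcomes are compared with no use of their own baselines at all. The document does not support that. The mixed ANOVA contains the baseline score as a time level, the Outcomes section speaks of change scores, and the GEE sensitivity analysis includes baseline. The accurate statement is narrower: no planned model uses the own baseline as a covariate.

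A reader might also infer an unconditional large loss of power. That fails too. In a pre/post mixed design the usual treatment test is group by time, which subtracts baseline. On that reading the loss against own-baseline ANCOVA is about 7 points at r = 0.7 and 4 at r = 0.8. At r = 0.5 that contrast does no better than stratum-only ANCOVA. The 27–33% figures hold only if the group main effect is read, and the section does not say that it is.

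The covariate for rows a to h is partly inferred. Table 3 names none, and the abstract sentence could be a summary of the primary analysis. A condensed article may leave covariate lists to a fuller document. But the sentence follows directly on the list of secondary outcomes and says positively that the stratum is the only covariate. The conflict between Table 3 and the Secondary Analysis section stands under either reading.

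Two further points stand. The groups are randomized, so precision is at issue rather than bias. And fast gait speed (row a) is close to the stratification variable, so the argument that the stratum says little about the outcome is weaker there; endurance and balance may also relate to gait speed more closely than quality of life does.

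**Conclusion.** The point holds as an inconsistency with an avoidable loss of precision. The secondary analysis is not fixed: Table 3 with the abstract gives ANCOVA on the stratum, and the Secondary Analysis section gives a time-by-group ANOVA without the stratum and without a named deciding effect. Neither conditions on the own baseline that Table 2 schedules.

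Under the stated assumptions, if the ANCOVA is used, omitting own baseline costs roughly 10 points of power or less at a correlation of 0.5, but over 20 points at 0.7 and about 35 at 0.8. If the baseline-to-T2 contrast of the mixed ANOVA is used, the cost is modest at high correlation and about 13 points at 0.5. If the group main effect is read, the cost is large throughout. The document supplies none of these correlations, so the figures are a range and not an estimate for this trial. The validity of the randomized comparison is not in question.

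**What to change.** Reconcile the abstract, the Secondary Analysis section and Table 3 to one model for rows a to h. Suggested wording: *T2 and T3 scores will be compared by ANCOVA with treatment, the gait-speed stratum, and the participant's baseline score on the same measure as a continuous covariate.* One linear mixed model of T2 and T3 with the same terms would serve equally well. Make this the deciding analysis in place of the ANOVA that treats baseline as an outcome, and limit the abstract's sentence on covariates to match.

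The cost is about one degree of freedom per model and a wording change. No new data are needed, and any missing baseline scores fall under the multiple imputation already planned.

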**Discussion:**

In order to direct clinicians, patients, and other health decision-makers, there is a need for a head-to-head comparison of different approaches to active, task-related walking training after stroke. We hypothesize that outcomes will be optimized through the application of a task-related training program that is consistent with key motor learning principles related to practice, guidance and feedback.

**Trial Registration:**

ClinicalTrials.gov # NCT00561405

## Background

Every year an estimated 9 million new stroke events occur globally, and an additional 30.7 million individuals live with the ongoing effects of stroke [1]. Decreased ability to walk is one of the most common and debilitating functional limitations following stroke [2-4]. Although the majority of adults with history of stroke recover some ability to ambulate independently following rehabilitation [2], many individuals experience long term residual limitations in walking speed [5,6], endurance [6] and walking-related self-efficacy [7,8]. Between 27% and 50% of community dwelling individuals report difficulty walking outside of their homes for months and years following stroke onset [6,9-11]. In the face of these difficulties, independent walking remains one of the most frequently-stated goals of stroke rehabilitation [12], with 75% of individuals identifying the ability to walk in the community as a priority in living at home [10]. Given these challenges, stroke-rehabilitation clinicians and researchers are compelled to apply and evaluate interventions that optimize the recovery of walking skill and participation in community mobility related activities.

According to recent stroke-rehabilitation reviews and practice guidelines, optimal walking recovery may be realized through the application of a task-related walking training approach [13-15]. In the literature, the term task-related walking practice generally refers to any intervention where walking or walking-related tasks are practiced using a functional approach [16]. Alternate terms include task-specific [13,17], task-oriented [18,19], and task practice [14,20,21]. Although the specific content of interventions varies, they are all based on the premise that in order to optimally improve walking skill, one must practice walking. Training protocols include walking tasks performed overground, on a treadmill, or both. Two of the most common interventions described in the stroke-rehabilitation literature include practice of a variety of primarily overground walking-related tasks [16], and body-weight-supported treadmill training (BWSTT) [22].

### Varied Overground Walking-task Training

Rooted in movement science, including motor learning research, Carr and Shepherd were early advocates of task-related walking practice after stroke [23]. They emphasized the importance of patient engagement in abundant, active practice of the whole task of walking. In addition, they promoted the practice of varied walking-related tasks organized in a circuit of stations. A small number of controlled studies have evaluated the effectiveness of this varied task practice approach in community-dwelling adults with stroke history [19,24,25]. These studies differ in quality, intervention content and effect on walking performance. In a small-sample pilot study by Dean and colleagues [24], 12 individuals with chronic stroke were randomized to a varied task-related training protocol, including overground walking, treadmill walking, and walking-related tasks (e.g. heel raises, step-ups, narrow base standing), or to a control intervention (upper- extremity task training). The experimental group improved walking endurance and speed more than the control group, however, the authors failed to discuss the implications of the relatively high proportion of participants who did not complete the study (n = 3). In a larger trial, 91 individuals within one year of stroke were randomized to receive 18 sessions of varied walking-related task practice, or upper-extremity task practice performed in sitting [19]. The experimental intervention included practice of walking tasks (i.e. stand up and walk, walking along a balance beam, walking backwards, walking while carrying, walking with speed, stairs and walking on a treadmill) and walking-related tasks (i.e. step-ups, kicking a ball). Following treatment, the walking group demonstrated significantly greater changes on the 6-minute walk test [35 m more than control, 95% confidence interval (CI) 7, 64], gait speed (0.11 m/s more than control, 95% CI 0.03, 0.19) and walking-related self-efficacy. In a more recent trial, 58 adults with chronic stroke were assigned to a 12-session walking-related task training protocol or to a non-exercise control intervention [25]. In this study, only 4 of the 15 stations involved walking while the remaining stations focused on strength and balance tasks in standing or sitting. The authors reported that the experimental group demonstrated modest, but statistically greater gains on the 6-minute walk test (19 m, p = 0.03) compared to the control group.

Based on this literature, variable practice of walking and walking-related activities in a circuit format is associated with greater improvements in gait speed, endurance and walking self-efficacy than a non-walking control intervention such as upper-extremity task practice. To date we do not know if this approach is superior to an alternate walking-focused treatment.

### Body Weight Supported Treadmill Training

BWSTT is rooted in the central pattern generator (CPG) theory of gait control and recovery [26]. The theory proposes that gait is largely controlled by a set of neurons located primarily at the spinal level [27], and these CPG's can be activated through the afferent input associated with typical gait through passive or assisted limb movements, weight shift, and postural alignment [26-28]. Mass repetition of these movements is thought to result in neural reorganization and subsequently improve capacity for over-ground walking in individuals with history of stroke [29,30]. As described in the literature, BWSTT requires the use of specialized body weight support equipment, a treadmill and the assistance of one to three trainers [22]. While recommended in opinion papers and reviews [31,32], when planning our study we found only 3 controlled trials that have evaluated the effectiveness of BWSTT in community dwelling individuals post-stroke [17,33,34]. In 2002, Sullivan randomized 24 individuals with chronic stroke to one of three BWSTT protocols; fast speed, variable speed and slower speed [33]. After 12 sessions, participants who trained at fast speeds improved overground velocity by 0.08 m/s more than those who trained at slow speeds (p = 0.04). In a larger RCT, 80 individuals with chronic stroke were assigned to one of the four combined treatment protocols; BWSTT and arm ergometer, cycling and arm ergometer, BWSTT and lower extremity strength training, and BWSTT and cycling [34]. The group that received alternating sessions of BWSTT and arm-ergometer exercise (12 sessions each over 6 weeks) improved overground gait speed by 0.12 m/s (p < 0.01) more than those who received the cycling and arm-ergometer program. There were no significant differences between the change scores of the different BWSTT interventions. Finally, in a recent repeated-measures, randomized crossover study [17], 20 adults with chronic stroke and recently discharged from physical therapy were assigned to receive either 12 sessions of BWSTT followed by 4 weeks of no treatment, or 4 weeks of no treatment then 12 sessions of BWSTT. Improvements in gait speed, gait efficiency (O_2 _cost) and daily stepping activity were observed after BWSTT treatment periods and not following the no-treatment periods. Based on these small-sample controlled trials, approximately 12 sessions of BWSTT seems to be more effective than a no-treatment control intervention or a non-walking intervention such as cycling. In addition, improvements seem to be optimized when participants train at speeds greater than their typical overground walking speeds. To date the effectiveness of BWSTT has not been evaluated against an alternate program of overground walking-focused training in community dwelling adults with history of stroke.

In summary, varied overground-focused walking practice and BWSTT have been shown to result in greater improvements in walking speed, endurance and/or self-efficacy when compared to non-walking interventions (i.e. arm and hand exercises, cycling). These two walking-task related interventions are different in theoretical rationale as well as in content. In the case of BWSTT, the rationale is clear - repetition of the normal stepping pattern of gait activates the locomotor CPG's and results in improved overground walking. Practice is constant and blocked, guidance is provided liberally, and the use of the treadmill environment allows for the repetition of a more normal gait pattern thought to be necessary to activating the CPG's [17,33,34]. In varied overground-focused walking practice, the theoretical premises for learning are less defined. While all studies implicitly apply the motor learning principle of specificity of practice, these overground-focused walking task training interventions fail to take full advantage of decades of behavioral motor learning research that have identified optimal learning conditions in healthy adult and rehabilitation populations [35]. For example, based on this research, retention and transfer of learned skills are typically enhanced if practice is abundant, variable, and organized in a random rather than blocked order. Learning is typically optimized if augmented feedback is delayed and intermittent rather than immediate and continuous and if physical guidance is not excessive but allows learners to experience and attempt to correct their own errors. Although the overground-focused task-related training interventions include variable practice of walking tasks that resemble typical walking conditions, order of practice is blocked, and feedback schedule is not described [19,24,25]. We suggest that the impact of task-related walking training will be more fully realized if the content and structure of interventions are consistent with these key motor learning principles.

The purpose of this randomized controlled trial is to compare the impact of the Motor Learning Walking Program (MLWP), a 15-session program of varied overground walking-task training consistent with key motor learning principles related to practice, guidance and feedback, to 15 sessions of BWSTT on walking performance in community-dwelling, ambulatory adults within 12 months of stroke onset.

It is our hypothesis that participants assigned to the MLWP group will demonstrate greater scores in comfortable gait speed and secondary outcome measures at post intervention and follow-up assessments.

